**Discussion:**

The implantation of a subdural EEG grid electrode in patients with aSDH is expected to be effective in diagnosing seizures in a timely manner, facilitating treatment with ASDs and monitoring of treatment success. Moreover, the occurrence of epileptiform discharges prior to the manifestation of seizure patterns could be evaluated in order to identify high-risk patients who might benefit from prophylactic treatment with ASDs.

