## Background

Epileptic seizures are one of the frequent complications seen in patients with traumatic brain injury; the incidence is approximately 20% [1]. In particular, acute subdural hematoma (aSDH) is one of the most important predictors for seizures—alongside other parameters like age, preoperative Glasgow Coma Scale score, cerebral herniation, hematoma volume, and time to operation—associated with worse neurological outcome [2–8]. In a recent systematic review, the mean incidence of seizures in aSDH was 28%, whereas one retrospective study focusing on diagnostic electroencephalography (EEG) reported a very high incidence of epileptiform discharges on surface EEG scans in 87% of patients with aSDH. Thus, the question arises as to whether the incidence of seizures is underestimated [8, 9].

Despite the successful evacuation of subdural hematoma, approximately one third of patients show no clinical improvement without any medical explanation as to why. Surface spot EEG is routinely performed to detect seizures; however, the sensitivity of this approach is limited due to the skin–bone barrier and the short duration of recording. Furthermore, surface EEG is not always available as a diagnostic tool—for example, during the night or on weekends—which is an additional limitation leading to lengthier time to treatment. Spot surface EEG only records for 20 to 30 min in contrast with continuous EEG recordings which are performed for hours or days.

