**Fig. 3 Fig3:**
[figure not shown]
**a** Postoperative scout of CT scan with frontal EEG electrodes. **b** Coronary reconstruction of the CT scan. **c** Postoperative scout of CT scan with temporal EEG electrodes. **d** 3D reconstruction of the CT-scan

As a clinical parameter, GCS will be evaluated every day and surface EEG will be performed at least once during the first 7 days post-operation in all patients. Additional surface EEGs will be performed if there is a suspicion of seizure. In the intervention arm, the continuation of invasive EEG monitoring will be evaluated by a board-certified epileptologist (Fig. 4). If a seizure is detected on EEG, treatment with benzodiazepines and ASDs will be started under further EEG monitoring and in consideration of the patient’s clinical condition. Treatment with ASDs will be adjusted on demand according to clinical and EEG assessment. If treatment with benzodiazepines and intravenous ASD is deemed insufficient for seizure suppression, escalation of treatment with anesthetics to obtain a seizure suppression or burst suppression pattern under EEG monitoring would be considered. The maximum period of invasive monitoring is set at 7 days, at which point the electrode should be removed. The subdural EEG electrode is removed simply by drafting as a normal wound drain and the incision sutured with Premilene 3.0 (Braun Melsungen AG OPM, D-34212 Melsungen, Germany).

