### Timeline

The anticipated timeline for study participants is as follows:
Patient admission with aSDHInformed consent obtained (interventional arm/control arm)Operative treatment of hematoma via craniotomy/craniectomy either with or without placement of subdural EEG electrodeMonitoring in intensive care unitPostoperative CT control 24 h laterClinical assessment as part of the routine standard of care (e.g., GCS, neurological status, routine laboratory tests)Three to seven days of invasive EEG monitoring by a board-certified epileptologistOptional spot surface EEG, usually between Days 1 and 7Removal of subdural EEG electrode at Day 7Patient discharge after clinical evaluationOutpatient clinical evaluation at 6 months postoperatively.Evaluation of chronic epilepsy at follow-up in 2–4 years

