### Statistical analysis and sample size

The IBM SPSS Statistics version 25 software program (IBM Corp., Armonk, NY, USA) will be used for data analysis. Data will be described using means ± standard deviations and numbers of patients, including percentages for continuous and categorical variables. For parametric parameters, an unpaired t-test will be used. For nonparametric parameters, variables will be analyzed in a contingency table using either Fisher’s exact test or the chi-squared test as appropriate. To assess the impact of the variables, odds ratios with 95% confidence intervals will be calculated. A *p*-value of 0.05 or less is considered to be statistically significant and all tests will be two-tailed.

When estimating the sample size with consideration of increased seizure detection by invasive EEG monitoring, the difference in the incidence rate is assumed to be 20%. The sample size was calculated as 110 patients (*n* = 55 patients each arm) to ensure 80% power (1-ß = 0.8). Moreover, time-to-event analysis will be performed to detect the timeline until seizure detection.

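### The only methods named for seizure predictors are unadjusted; if the arms are pooled, any variable recorded at different rates by arm gets a distorted odds ratio

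*Protocol article*

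**What the plan says.** In the Protocol article, the section Trial outcomes measures lists predictors of early and late seizures among the secondary outcomes. It names no candidate variables and does not limit the analysis to one arm.

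Statistical analysis and sample size gives the methods. Continuous variables get an unpaired t-test. For the others, "variables will be analyzed in a contingency table using either Fisher’s exact test or the chi-squared test as appropriate". Then: "To assess the impact of the variables, odds ratios with 95% confidence intervals will be calculated". A time-to-event analysis of seizure detection is also planned. No arm term, stratification or multivariable model is mentioned.

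The same section bases the sample size on better detection by invasive EEG: "the difference in the incidence rate is assumed to be 20" percent.

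Recording differs by arm. The Timeline gives "Three to seven days of invasive EEG monitoring", which only the intervention arm can have. Under Trial interventions, after the caption of Fig. 3, "surface EEG will be performed at least once during the first 7 days post-operation in all patients", with more on suspicion of a seizure. The Background notes: "Spot surface EEG only records for 20 to 30 min".

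The Discussion part of the Abstract raises a use for discharges: "the occurrence of epileptiform discharges prior to the manifestation of seizure patterns could be evaluated in order to identify high-risk patients". The purpose given there is to find candidates for preventive antiseizure medication.

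**The concern.** A predictor analysis asks whether a variable is related to having seizures. A crude table over both arms asks whether it is related to detected seizures in a mixture of two groups that the plan itself expects to differ in detection. If the variable is also recorded more often in one arm, arm produces an association between the two even where none exists within either arm.

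Discharges are the obvious candidate: days of subdural recording will show more of them than a short surface recording, if detection depends on recording time and site. A marker of having been monitored invasively could then look like a marker of seizure risk. The Abstract links this marker to choosing patients for prophylaxis, so a false or inflated association would matter.

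**Working it through.** **The plan's own figure.** The plan gives no figure for the predictor analysis. Its total of 110 (55 per arm) rests on a 20-point difference, 80% power and two-sided 0.05, with no baseline rate stated. By the pooled normal-approximation formula, 7% vs 27% needs exactly 55 per arm and 28% vs 48% needs 92. The point does not depend on which rate was used, so both pairs are shown below.

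**Inputs**
- 55 per arm, two-sided 0.05, 20-point difference (read as absolute): Statistical analysis and sample size.
- Seizures 28% vs 48%: the 28% is the mean incidence from the systematic review cited in the Background, plus 20 points. Seizures 7% vs 27%: the pair that reproduces 55 per arm. Neither is stated as the planning rate.
- Marker rates by arm: assumptions, varied. The 87% is borrowed from the Background, which reports a "very high incidence of epileptiform discharges on surface EEG scans in 87% of patients with aSDH". It is a surface-EEG figure.
- Marker and seizure independent within each arm, so the true within-arm odds ratio is 1.

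**Closed form.** Let p be the seizure rate and m the marker rate, with subscripts C (control) and I (intervention). With equal arms the pooled cells are proportional to:
- A (marker, seizure) = m_C p_C + m_I p_I
- B (marker, no seizure) = m_C(1−p_C) + m_I(1−p_I)
- C (no marker, seizure) = (1−m_C)p_C + (1−m_I)p_I
- D (neither) = (1−m_C)(1−p_C) + (1−m_I)(1−p_I)

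Crude odds ratio = AD/BC.

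For seizures 28% vs 48% and marker 30% vs 87% (control vs intervention):
- A = 0.084 + 0.4176 = 0.5016
- B = 0.216 + 0.4524 = 0.6684
- C = 0.196 + 0.0624 = 0.2584
- D = 0.504 + 0.0676 = 0.5716
- AD/BC = 0.2867/0.1727 = 1.66

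**False-positive rate of the pooled uncorrected chi-squared test.** Simulated, 40,000 trials per row:

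| Marker, control vs intervention | Seizures 28% vs 48%: crude OR, rejection | Seizures 7% vs 27%: crude OR, rejection |
|---|---|---|
| 30% vs 30% | 1.00, 5.2% | 1.00, 5.2% |
| 30% vs 50% | 1.19, 7.5% | 1.34, 9.4% |
| 30% vs 70% | 1.41, 14.1% | 1.78, 20.1% |
| 30% vs 87% | 1.66, 24.1% | 2.48, 36.2% |
| 60% vs 87% | 1.35, 10.1% | 1.72, 11.1% |
| 87% vs 95% | 1.24, 5.6% | 1.47, 1.8% |

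Fisher's test is somewhat lower: about 20% for 30% vs 87% and 6% for 30% vs 50%, with seizures 28% vs 48%.

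The last row has few false positives because few patients lack the marker: 55 × 0.13 + 55 × 0.05 = 9.9 expected. The estimate is still off 1.

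**With stratification by arm.** In a companion set of 20,000-trial runs (control vs intervention seizure pairs 5% vs 25%, 8% vs 28%, 20% vs 40% and 28% vs 48%, each with seven marker pairs), a Mantel-Haenszel test stratified by arm rejected in 4.6% to 5.5% of trials throughout.

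**Baseline variable, for illustration.** A factor unrelated to seizures, present in 60% of controls and 40% of the intervention arm (assumed), with seizures 28% vs 48%, gives (0.36 × 0.60)/(0.64 × 0.40) = 0.84. With equal frequency in both arms it gives 1.00.

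**The case against.** The strongest reply is that the article never says the arms are pooled. The methods paragraph is generic and is not tied to the predictor outcome. This is a condensed article, and an analysis plan that is not shown may contain an adjusted model. That stands as far as it goes: pooling is inferred from unrestricted wording, and the absence of an arm term is not by itself an error.

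A reader might go further and infer that the plan commits to testing discharges as a predictor in a pooled crude table. The documents do not support that. Discharges as a risk marker appear only as something that could be evaluated, directly after a sentence about the implanted electrode, and may concern the intervention arm alone. The section Clinical and morphological parameters lists no EEG marker, although time to first interictal discharge is a secondary measure, so discharges will be recorded.

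A reader might also infer that all seizure predictors are biased. That is not supported either. Age, GCS or hematoma volume are distorted only if the nonrandomized arms differ on them. Allocation follows consent and device availability. The article concedes possible selection bias but shows no such imbalance.

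Finally, the larger false-positive rates rest on assumed discharge rates, with a surface-EEG figure applied to the subdural arm. If surface EEG already finds 87% and invasive EEG 95%, they fall to about 2% to 6%. The crude odds ratio then still centres on 1.24 to 1.47 instead of 1, but the evidence for a serious error is weak.

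What remains is that the methods the section does name, applied to an outcome it does not restrict by arm, perform worse than an alternative that costs almost nothing.

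**Conclusion.** The point holds conditionally and is minor. If predictor odds ratios are computed with the arms pooled, the unadjusted methods named in the article are biased for any variable whose recorded frequency differs by arm, given the plan's own 20-point difference in detected seizures. For discharges the distortion runs from none (equal rates) through an odds ratio of 1.19 with about 7.5% false positives (50% vs 30%) to 1.66 with about 24% (87% vs 30%), with seizures 48% vs 28%. At 27% vs 7% the last case reaches 2.48 and about 36%. Which of these applies cannot be settled from the article, since it gives no discharge rates by arm.

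Two limits apply. The electrode is out by day 7, so the detection argument concerns seizures in the monitored period; the article states no arm difference for late seizures. Separately, the seizure definition includes clinical suspicion with interictal discharges, so discharges overlap with the outcome itself, and an arm term does not remove that. The primary comparison is not affected.

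**What to change.** Add a sentence to Statistical analysis and sample size: odds ratios for predictors of seizures are estimated within arm, by Mantel-Haenszel stratified by study arm or by logistic regression with arm as a covariate; predictors derived from the EEG are analysed in the intervention arm only, where all patients have the same type of recording. If the full analysis plan already says this, the article only needs to agree with it.

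No new data are needed, because arm is known for every patient. The cost is precision for EEG-derived predictors, which would rest on about 55 patients instead of 110. If both arms were equally informative, intervals on the log scale would be about √(110/55) = 1.41 times as wide. The overlap between discharges and the seizure definition needs its own statement, for example a predictor analysis that counts only clinical or ictal-pattern seizures.

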### Trial outcomes measures

The primary and secondary outcome measures for this study are as follows:

Primary outcome measure:
Incidence of seizure and time between surgery and seizure detection

Secondary outcome measures
Functional and neurological outcomes (e.g., modified Rankin scale, Glasgow outcome scale) at discharge and for 3 to 6 months postoperativelyTherapeutic effects and benefits attributable to invasive monitoring and ensuing treatment (time to first interictal epileptiform discharges, occurrence of seizure patterns and progression of seizures to status epilepticus)Complication rate of the interventionPredictors for the development of early and late epileptic seizuresLongterm Follow-up for evaluation of chronic epilepsy (2–4 years)

All measures will be performed by the staff members of DISEASE-tiral. Independent from the study, all patients are scheduled for an outpatient clinic appointment in 6 months for clinical follow-up. Otherwise, the follow-up data will be retrieved by a phone call from the responsible study investigators. The long term follow-up will be performed accordingly.

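### If discharges before a seizure are tested as a seizure predictor with the association methods the protocol states, the odds ratio is biased by unequal exposure windows and its sign cannot be interpreted

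*Protocol article*

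**What the plan says.** The Discussion part of the protocol article's abstract says that "the occurrence of epileptiform discharges prior to the manifestation of seizure patterns could be evaluated in order to identify high-risk patients", with a view to prophylactic treatment.

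The section on trial outcome measures lists, as secondary outcomes, predictors of early and late seizures (no candidates named) and, under therapeutic effects, "time to first interictal epileptiform discharges, occurrence of seizure patterns and progression of seizures to status epilepticus".

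The section on statistical analysis and sample size names an unpaired t-test and then says that "variables will be analyzed in a contingency table using either Fisher’s exact test or the chi-squared test as appropriate". It continues: "To assess the impact of the variables, odds ratios with 95% confidence intervals will be calculated". Separately, "time-to-event analysis will be performed to detect the timeline until seizure detection".

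The article gives no landmark, time-dependent covariate or common exposure window. The seizure definition has three routes: a documented clinical seizure, an ictal EEG pattern, or clinical suspicion together with interictal discharges.

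**The concern.** The wording in the abstract makes the exposure a discharge that comes before the seizure. In a two-by-two table, a patient who seizes on day 1 had at most one day in which to become exposed. A seizure-free patient had the whole recording, which the article puts at three to seven days. Exposure time then depends on the outcome. This is a time-window bias of the immortal-time type, and it pushes the odds ratio below 1 for a marker that has nothing to do with seizures. It remains when the analysis is confined to the electrode arm, the only arm with continuous recording.

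The result could bear on who is later considered for prophylaxis. An unrelated marker could look protective, and a real one could look null or protective.

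**Working it through.** **Inputs.** From the article: 28% seizure incidence and 87% discharge prevalence (Background); a 20-point difference and 55 patients per arm (sample size paragraph); recording of at most 7 days (Trial interventions). Assumed: 48% seizures with the electrode (28% + 20 points), 50% as a lower discharge prevalence, and every onset pattern below. The article gives no figure for this question to reproduce. The 55 per arm serves only as the number of monitored patients.

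**Null marker, constant hazards, 7 days.**

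- Seizure rate: −ln(0.52)/7 = 0.0934 per day.
- Discharge rate: −ln(0.13)/7 = 0.2915 per day.
- P(seizure by day 7 with no earlier discharge) = 0.0934/(0.0934 + 0.2915) × (1 − 0.52 × 0.13) = 0.2427 × 0.9324 = 0.2263.
- P(discharge before seizure, given seizure) = (0.48 − 0.2263)/0.48 = 0.529.
- P(discharge, given no seizure) = 0.87.
- Odds ratio = (0.529/0.471)/(0.87/0.13) = 1.123/6.692 = 0.17.

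With no true association, the odds ratio should be 1. Other scenarios, and the rate at which Fisher's test is significant (two-sided 0.05) in simulated trials of 55:

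| Seizures | Discharges | Null odds ratio | Fisher significant |
|---|---|---|---|
| 28% | 50% | 0.36 | 31% |
| 28% | 87% | 0.18 | 64% |
| 48% | 50% | 0.34 | 42% |
| 48% | 87% | 0.17 | 76% |

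With discharge prevalence from 30% to 87%, the null odds ratio is 0.08–0.60 when seizures, discharges or both are front-loaded, and 0.14–0.63 when recording varies between 3 and 7 days.

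**Early discharge onset.** Keep 48% seizures at constant hazard. Let a share of dischargers start uniformly within 6 hours and the rest uniformly over 7 days. Among seizure patients, the seizure precedes an early-starting discharge with probability 0.024, and a discharge spread over the week with probability 0.554. With 80% early, P(discharge before seizure, given seizure) = 0.87 × (0.8 × 0.976 + 0.2 × 0.446) = 0.757, so the odds ratio = (0.757/0.243)/6.692 = 0.47.

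| Discharges | Share early | Null odds ratio | Fisher protective |
|---|---|---|---|
| 87% | 80% | 0.47 | 14% |
| 87% | 90% | 0.61 | 7% |
| 87% | 100% | 0.84 | 2% |
| 50% | 80% | 0.77 | 5% |

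If every discharge is present when recording starts, the bias is zero.

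**Opposing force from the seizure definition.** Suppose a fraction f of cases qualifies only through suspicion plus discharges. They are exposed by definition, so the exposed share of cases becomes f + (1 − f)p. At 28% seizures and constant hazards, the null odds ratio returns to 1 when:

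- 50% discharges (p = 0.265): f = (0.50 − 0.265)/(1 − 0.265) = 0.32
- 87% discharges (p = 0.551): f = (0.87 − 0.551)/(1 − 0.551) = 0.71

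Above those shares, an unrelated marker looks harmful.

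**A real marker.** If a discharge triples the seizure hazard (constant hazards, rate before discharge set to 28% over 7 days), the table's odds ratio is 0.66 at 87% discharges and 1.24 at 50%.

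**Alternatives under the null, n = 55.** A time-dependent Cox score test rejects in 4–5% of trials, and a 24-hour landmark table with Fisher's test in 1–3%. Counting discharges over the full recording for everyone also gives a null odds ratio of about 1.0 (1.02–1.14 with 3–7 day recording), but it includes discharges after the seizure and after treatment has begun, so it no longer answers the question raised in the abstract.

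**The case against.** A reader might infer that the article commits to judging the discharge marker by odds ratios. It does not. The sentence on odds ratios is general, the predictor outcome names no candidates, discharges are not among the listed clinical and morphological parameters, and the abstract speaks only of what could be evaluated. For baseline predictors such as age or admission GCS, an odds ratio has no such bias. Time to first discharge is listed as an outcome, and nothing forbids a covariate in the planned time-to-event analysis. An article may also leave the handling of a time-varying marker to a fuller document. All of this stands, so the point is conditional.

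A reader might also infer that a useless marker must look strongly protective. The documents do not support that either. The constant-hazard case puts median discharge onset at ln 2/0.2915 = 2.4 days, for which the article offers no evidence. With early onset the distortion is modest, and the third seizure route works against it.

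What remains is that the methods the article does state for relating a yes/no variable to an outcome do not suit the exposure it describes. Two opposing artefacts of unknown size do not make the odds ratio readable.

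**Conclusion.** The point holds in conditional form. If discharge before seizure is cross-tabulated against seizure, the odds ratio for an unrelated marker is biased below 1. With 87% discharges and 48% seizures over 7 days, it ranges from 0.17 (constant hazards; about 76% of trials of 55 significantly protective) through about 0.5–0.8 (80–100% of dischargers starting within 6 hours; 14% down to 2%) to no bias when all discharges are present at the start. These figures assume an unrelated marker and outcomes that do not depend on discharges. Under the article's own seizure definition, some cases are exposed by definition, so neither the size nor the direction of the odds ratio can be interpreted. The matter is secondary and exploratory, and the primary outcome is unaffected. Because the remedy is simple and the data are already planned, the change is worth making.

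**What to change.** Add a sentence to the statistical analysis section along these lines: if discharges are assessed as a seizure predictor in the electrode arm, first discharge will enter as a time-dependent covariate in a Cox model for time from surgery to first ictal pattern or clinical seizure, not counting seizures that qualify only through interictal discharges. Alternatively, name a common landmark: for example, discharges in the first 24 hours against later seizures, among patients seizure-free and still recorded at 24 hours. Either should replace an odds ratio of discharge before seizure.

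The cost is that sentence. The outcome list already includes "time to first interictal epileptiform discharges", and the timing of seizures is among the parameters to be collected, so no new data are needed. The landmark version drops patients who seize before the landmark.

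### The 80% power claimed for 55 patients per arm rests on an unstated control rate; at the seizure incidences the protocol itself cites, power for a 20-point difference is about 51% to 64%

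*Protocol article*

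**What the plan says.** All of the planning inputs stand in the protocol article under *Statistical analysis and sample size*. There "the difference in the incidence rate is assumed to be 20" per cent, which the text explains by better seizure detection with invasive EEG. "The sample size was calculated as 110 patients", 55 in each arm, "to ensure 80% power". For significance, a p-"value of 0.05 or less is considered to be statistically significant", and "all tests will be two-tailed". Contingency tables are to be tested with Fisher's exact test or the chi-squared test. A time-to-event analysis is added.

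The paragraph names no seizure rate for either arm. The only seizure incidences in the article are in the *Background*. For acute subdural hematoma, a systematic review found that "the mean incidence of seizures in aSDH was 28" per cent. Seizures are also described as "one of the frequent complications seen in patients with traumatic brain injury; the incidence is approximately 20" per cent. The same section asks whether the incidence of seizures is underestimated.

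**The concern.** A difference between two proportions does not determine a sample size. The variance depends on where the two rates lie, so 20 points from a very low rate needs far fewer patients than 20 points from a rate near 30%. As written, the 80% cannot be checked from the paragraph, and the reader will turn to the incidences given in the *Background*.

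Incidence of seizures is part of the primary outcome, and the paragraph presents the 80% as assured. If true power is nearer one half, the study would miss a real 20-point difference in four to five of ten repetitions, while the reader is told two in ten. A non-significant result would then carry much less information than the protocol suggests.

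**Working it through.** **Inputs.** Two-sided alpha 0.05, 55 per arm, 1:1, target power 80%, difference 20 points: all from *Statistical analysis and sample size*. Control rates 28% and 20%: from the *Background*, used here as assumptions. They are assigned to the control arm because the paragraph ascribes the difference to increased detection in the invasive-EEG arm.

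**Formula** (pooled variance, per arm), with p̄ = (p1 + p2)/2:

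n = [1.960·√(2p̄(1−p̄)) + 0.842·√(p1(1−p1) + p2(1−p2))]² / (p2 − p1)²

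**Step 1: which rates reproduce 55?** For 7% vs 27%, p̄ = 0.17:

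n = [1.960·√0.2822 + 0.842·√0.2622]² / 0.04 = (1.041 + 0.431)² / 0.04 = 54.2, so 55.

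The stated figure is therefore recovered at a control rate of about 7%. The article gives no such rate.

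**Step 2: the cited rates.**

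- 28% vs 48%, p̄ = 0.38: n = [1.960·√0.4712 + 0.842·√0.4512]² / 0.04 = (1.345 + 0.565)² / 0.04 = 91.3, so 92 per arm (184 in total).
- 20% vs 40%, p̄ = 0.30: n = [1.960·√0.42 + 0.842·√0.40]² / 0.04 = (1.270 + 0.532)² / 0.04 = 81.2, so 82 per arm (164 in total).

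**Step 3: exact power at 55 vs 55.** This sums the probability of every pair of binomial counts for which the test gives p ≤ 0.05.

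| Control vs intervention | n per arm for 80% (formula) | Chi-squared power | Fisher power |
|---|---|---|---|
| 28% vs 48% | 91.3 | 59.1% | 50.5% |
| 20% vs 40% | 81.2 | 63.9% | 56.0% |
| 10% vs 30% | 61.6 | 77.2% | 68.2% |
| 8% vs 28% | 56.7 | 80.9% | 72.3% |
| 7% vs 27% | 54.2 | 82.8% | 74.7% |
| 5% vs 25% | 48.8 | 87.3% | 80.1% |
| 67% vs 87% | 68.3 | 72.1% | 63.6% |
| 73% vs 93% | 54.2 | 82.8% | 74.7% |
| 75% vs 95% | 48.8 | 87.3% | 80.1% |

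Power for a fixed difference is symmetric: p1 vs p2 gives the same result as 1−p2 vs 1−p1. So 80% is reached at control rates of about 8% or lower with chi-squared (about 5% with Fisher), and again at about 72% or above with chi-squared (about 75% with Fisher).

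**Step 4: other methods at 28% vs 48%.** None gives 55 per arm: continuity correction 102, unpooled variance 89, arcsine 91, one-sided 72 (64 one-sided at 20% vs 40%). A log-rank test with constant hazards (hazard ratio ln 0.52 / ln 0.72 = 1.99; 55 × 0.76 = 41.8 expected events) has about 60% power. Reading the 20% as a relative increase (28% vs 33.6%) would need 1066 per arm.

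**Step 5: what 55 per arm can detect from a 28% control rate.** Chi-squared: 28% vs 54%, 79.9% power, so about 26 points. Fisher has 73.4% power there and needs 28% vs 56% (79.7%), so about 28 points.

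**Step 6: precision at 28% vs 48%.** 95% half-width = 1.96·√[(0.2016 + 0.2496)/55] = 0.178, about 18 points.

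**The case against.** The strongest reply is that 28% is a literature figure used to motivate the study, not a labelled planning rate. The assumed rates may stand in a full protocol that is not shown, and an article may condense them. This stands as far as it goes: a reader might infer that the calculation was done wrongly and that the trial is underpowered whatever the true rates are, but the article does not prove that. The shortfall is conditional on a control rate near those cited. Even so, any omitted rate that reproduces 55 per arm would have to lie far from every seizure incidence the article reports.

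One reading does use the 28% and comes close. If 28% is the intervention rate and 8% the control rate, chi-squared power is 80.9%. But no 8% appears anywhere, Fisher's test then has only 72.3%, and the reading has invasive monitoring finding no more than the published incidence. That conflicts with the argument for increased detection and with the concern about underestimation.

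A reader might also infer that only a very low control rate can support the claim. That is not so, because high rates do so too. The *Background* does give 87%, but for epileptiform discharges on surface EEG, not for seizures. Taking 87% as the upper rate (67% vs 87%) gives only 72.1% and 63.6%.

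Finally, this is a single-centre, nonrandomized phase I study that also has time to detection in its primary outcome, and a randomized trial is hoped for afterwards. This limits the consequences, and it would be speculation to say that a null result will be taken as evidence against invasive monitoring. It does not make the 80% right: the article chose to state a powered comparison, and the time-to-event analysis does not restore the power (about 60% in Step 4).

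**Conclusion.** The point holds conditionally. With the control rate at the article's own figures, 55 per arm does not give 80% power for a 20-point difference: power is about 59% (chi-squared) or 51% (Fisher) at 28% vs 48%, and about 64% or 56% at 20% vs 40%. The shortfall is roughly 16 to 30 percentage points of power, or 37 (92 − 55) and 27 (82 − 55) patients per arm.

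This assumes that the 20% is an absolute difference, that the published incidence belongs to the control arm, equal arms, two-sided 0.05 and no dropout. The first of these is favourable to the plan. As no control rate is stated, the supportable conclusion is that the power claim is inconsistent with the incidences in the same document and cannot be verified from it. It should be corrected, since the primary comparison relies on it and the correction is cheap.

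**What to change.** Revise the sample-size paragraph so that it gives both assumed seizure rates, their source and the test used. Keep the 110 patients and restate what they provide, for example:

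> With 55 patients per arm and a two-sided 5% level, power for 28% vs 48% is about 59% (chi-squared test) or 51% (Fisher's exact test). From a control rate of 28%, the difference detectable with 80% power is about 26 percentage points (chi-squared) or 28 (Fisher).

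If other rates were in fact assumed, state and justify them, and explain why they differ from the incidences in the *Background*. In either case, report the difference in incidence with its 95% confidence interval (half-width about 18 points at 28% vs 48%), so that a non-significant result can be read for what it excludes.

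The cost is one rewritten paragraph and no additional patients. The drawback is that the stated power becomes less favourable.
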